## Abstract

**Background:**

There is a pressing need for greater attention to patient-centered health behavior and psychosocial issues in primary care, and for practical tools, study designs and results of clinical and policy relevance. Our goal is to design a scientifically rigorous and valid pragmatic trial to test whether primary care practices can systematically implement the collection of patient-reported information and provide patients needed advice, goal setting, and counseling in response.

**Methods:**

This manuscript reports on the iterative design of the My Own Health Report (MOHR) study, a cluster randomized delayed intervention trial. Nine pairs of diverse primary care practices will be randomized to early or delayed intervention four months later. The intervention consists of fielding the MOHR assessment – addresses 10 domains of health behaviors and psychosocial issues – and subsequent provision of needed counseling and support for patients presenting for wellness or chronic care. As a pragmatic participatory trial, stakeholder groups including practice partners and patients have been engaged throughout the study design to account for local resources and characteristics. Participatory tasks include identifying MOHR assessment content, refining the study design, providing input on outcomes measures, and designing the implementation workflow. Study outcomes include the intervention reach (percent of patients offered and completing the MOHR assessment), effectiveness (patients reporting being asked about topics, setting change goals, and receiving assistance in early versus delayed intervention practices), contextual factors influencing outcomes, and intervention costs.

**Discussion:**

The MOHR study shows how a participatory design can be used to promote the consistent collection and use of patient-reported health behavior and psychosocial assessments in a broad range of primary care settings. While pragmatic in nature, the study design will allow valid comparisons to answer the posed research question, and findings will be broadly generalizable to a range of primary care settings. Per the pragmatic explanatory continuum indicator summary (PRECIS) framework, the study design is substantially more pragmatic than other published trials. The methods and findings should be of interest to researchers, practitioners, and policy makers attempting to make healthcare more patient-centered and relevant.

**Trial registration:**

Clinicaltrials.gov: NCT01825746

## Background

There is significant interest in transforming health information technology to be more patient-centered [1-3]. To further integrate these movements toward patient-centeredness and information technology-supported healthcare, one key element that has been missing is a set of brief, practical patient-reported items that are relevant to and actionable by patients and their healthcare team [4,5]. In 2011, 93 national primary care, public health, health behavior, and psychosocial experts as well as patients engaged in a rigorous three-phase process to identify evidence-based, patient-reported measures that if routinely collected could be used to improve health and monitor health status [6]. The process included assembling all possible candidate measures, using a grid-enabled measures wiki platform to identify key measures for consideration [7], and a town hall meeting to finalize the measures. From this process, 17 brief, feasible screening questions evaluating 10 domains of health behaviors and psychosocial problems were identified [8].

Before these patient-reported measures are fully integrated into health risk assessments or routinely integrated into electronic health records (EHRs) and patient portals, research is needed to evaluate relevance, feasibility, and impact on care [9-11]. Randomized pragmatic implementation studies are one way to efficiently and rapidly make this evaluation [12]. Key to pragmatic studies is stakeholder involvement, of both clinicians and patients, and outcomes important to potential adoption settings. Table 1 summarizes the key characteristics of pragmatic trials compared to traditional efficacy trials in terms of measures, costs, focus and other dimensions. As shown, there are major differences in the formulation of study questions, methods issues receiving the greatest priority, outcomes and analysis, and level of stakeholder involvement. Despite the differences, if properly designed, both study designs can yield scientifically valid answers to posed research questions. The Consolidated Standards of Reporting Trials (CONSORT) group has also developed a reporting standard and a helpful summary figure, called the Pragmatic Explanatory Continuum Indicator Summary (PRECIS), to report the extent to which an intervention study is pragmatic versus explanatory on 10 dimensions [13,14].

**Table 1 T1:** Distinguishing differences between pragmatic and traditional clinical efficacy trials

	**Pragmatic study**	**Traditional clinical efficacy**
Stakeholder involvement	Engaged in all study phases including study design, conducting the study, collecting data, interpreting results, disseminating findings	Limited engagement, often in response to investigator ideas or study subjects
Research Design	Includes internal and external validity, design fidelity and local adaptation, real life settings and populations, contextual assessments	Focus on limiting threats to internal validity, typically uses randomized controlled trial, participants and settings typically homogenous
Outcomes	Reach, effectiveness, adoption, implementation, comparative effectiveness, sustainability	Efficacy, mechanism identification, component analysis
Measures	Brief, valid, actionable with rapid clinical utility, feasible in real world and low-resource settings	Validated measures that minimize bias, focus on internal consistency and theory rather than clinical relevance
Costs	Assessments include intervention costs and replication costs in relation to outcomes	Often not collected or reported
Data Source	May include existing data (electronic health records, administrative data) and brief patient reports.	Data generation and collection part of clinical trial
Analyses	Process and outcome analyses relevant to stakeholders and from different perspectives	Specified a priori and typically restricted to investigator hypotheses
Availability of findings	Rapid learning and implementation	Delay between trial completion and analytic availability

The purposes of this manuscript are to describe the background, engagement of stakeholders, characteristics of participating primary care practices, study design in relation to the pragmatic explanatory continuum, key outcomes, and automated tool and feedback system developed for the My Health Outcomes Report (MOHR) study.

## Methods

### Overall design

The MOHR study is a paired, cluster (practice level) randomized, non-blinded, practical, implementation study that uses a delayed intervention design with 9 pairs of primary care practices (18 total). The design combines elements of pragmatic trials, implementation science, systems science, and mixed methods approaches, and engages stakeholders as partners throughout the study design, implementation, evaluation and subsequent dissemination. One practice in each pair will be randomized to early implementation, and the second to delayed implementation four months later. Implementation will consist of each practice defining a patient population and workflow and then fielding the systematic collection of the patient reported measures in daily care. The primary outcomes will be implementation measures and costs that are relevant to potential adopting and funding agencies [15-19]. Patient goal-setting and clinical follow-up in the 10 health behavior and psychosocial domains will be compared between early and delayed intervention sites prior to implementation of the MOHR assessment in delayed intervention sites, thus delayed intervention practices effectively serve as control practices. Feasibility will be assessed by monitoring implementation in both early and delayed implementation sites (see Figure 1 for project overview and timeline). The project is funded through a unique partnership of grant supplementation from the National Cancer Institute (NCI), the Agency for Healthcare Research and Quality (AHRQ), and the Office of Behavioral Social Sciences Research (OBSSR).

**Figure 1 F1:**
[figure not shown]
**MOHR study overview and timeline.** The study started in January 2013. The approximate implementation date for the early implementation practices is March 2013 and July 2013 for the delayed implementation practices. (IRB = institutional review board, EIS = early implementation sites, DIS = delayed implementation sites).

### Research teams and study settings

To carry out this pragmatic trial, partnerships were created between local research teams at eight nationally distributed academic institutions that manage a practice-based research network (PBRN) or participate in the Cancer Prevention and Control Research Network (CPCRN) [20,21]. Given the network affiliations, each research team has expertise in partnering with their practice and patient stakeholders. Accordingly, research teams are charged with helping their partner practices implement the patient-reported assessment and carry out the MOHR study protocol, while balancing the need for adaptation to ensure implementation is relevant to local culture and practice flow (see ‘Balancing fidelity and adaption,’ below) [22]. To coordinate activities across the project, a MOHR planning committee composed of representatives from all local research teams and practices will have joint bimonthly meetings for planning (pre-implementation) and to share successes and challenges (post-implementation). The organization and coordination of activities is depicted in Figure 2.

**Figure 2 F2:**
[figure not shown]
**MOHR study organization and coordination.** The four general partners include funders, project coordination, local research teams, and study practices. The funders provide project coordinators general input into the study implementation and design. Overall project coordination includes the five working groups, MOHR planning committee, and the coordination center. The local research teams directly coordinate with the nine practice pairs to carry out and support the MOHR implementation and evaluation. (ACORN = Virginia Ambulatory Care Outcomes Research Network, UV = University of Vermont, UNC = University of North Carolina, UCLA = University of California, Los Angeles, and UTH = University of Texas Houston).

Research teams identified one or two pairs of primary care practices within their network that were similar with respect to practice type (*e.g.*, FQHC or PBRN, family practice or internal medicine), practice ownership, geographic region, EHR infrastructure, and patient population served. Practice pairs were purposefully selected to represent the diversity of primary care settings and populations to ensure greater generalizability of results. Practices were randomly allocated to the early or delayed condition by coin toss. To conceal allocation, the researchers randomizing practices *(i.e.*, project coordination members) were blinded to practice name; practices were labeled by number in paired blocks (by local research teams), and identity was revealed to all participants one week later during a joint call.

Table 2 presents the characteristics of the 18 participating practices. The PBRN practices tend to have higher proportions of insured patients and fewer ethnic minorities compared to the FQHCs. Most practices are small to medium in size, with one to six providers and seeing 1,500 to 10,000 unique adult patients annually. All practices, except two, have EHRs. While nearly half of practices have initiated or received patient-centered medical home designations, most report limited experience with behavioral health and varying levels of experience with quality improvement.

**Table 2 T2:** Participating practice characteristics

**Site**	**State**	**Setting**	**Patients seen per year**	**Provider FTEs**	**Rooming staff FTE**	**Patient ethnicity and race**		**Insurance type**		
						**Latino**	**Black**	**Medicare**	**Medicaid**	**None**
1	VA	S	5,000	2	4	15%	10%	5%	0%	30%
2	VA	S	1,500	1	2	20%	10%	1%	0%	9%
3	VA	R	2,500	1.6	7	1%	49%	12%	1%	49%
4	VA	S	5,200	4	11	2%	18%	15%	2%	18%
5	VA	U	3,700	5.9	17.3	2%	39%	24%	2%	39%
6	VA	U	3,400	5.3	16.9	1%	17%	26%	1%	17%
7	CA	R	3,500	5.5	15	3%	1%	13%	3%	1%
8	CA	R	5,400	7	25.5	13%	2%	12%	13%	2%
9	VT	R	9,500	5	13.5	1%	5%	13%	1%	5%
10	VT	R	10,000	5	14	1%	2%	15%	1%	2%
11	NC	R	1,100	4.5	12	2%	60%	49%	2%	60%
12	NC	R	7,500	3.5	10	40%	60%	10%	10%	70%
13	CA	U	2,040	1	7	75%	25%	5%	45%	50%
14	CA	U	2,180	2	6	75%	25%	5%	45%	50%
15	TX	R	4,800	2	6	48%	23%	2%	48%	23%
16	TX	R	3,800	2	6	23%	32%	2%	23%	32%
17	TX	U	2,800	3	19	82%	6%	1%	82%	6%
18	TX	U	2,800	3.6	12	80%	5%	1%	80%	5%

Notes:

Practices 1-10 belong to a practice based research network and practices 11-18 belong to the Cancer Prevention and Control Research Network.

All practices except Site 2 and 3 have an electronic health record.

All practices have experience with prior research or quality improvement projects.

*FTE* Full Time Equivalent.

*S* Suburban, *R* Rural, *U* Urban.

### Work groups

To facilitate rapid, collaborative decision making on important issues relevant to the MOHR study design and implementation, work groups were formed consisting of research team members, clinicians, funding agency representatives, and content experts. Each work group is responsible for effectively solving issues related to their specific MOHR study area and bringing proposals to the larger collaborative for approval. Work groups include: Web Tool and Practice Training Work Group – to design and test an electronic version of the comprehensive behavioral and psychosocial risk assessment, http://www.MyOwnHealthReport.org, for practices to use and to create training sessions to prepare practices to address topics identified by the MOHR assessment; Patient Experience Survey Work Group – to design the Patient Experience Survey (see ‘Outcomes assessment’ , below) for assessing main patient-level outcomes; Clinical Context Work Group – to identify and evaluate how key practice, patient, and environmental contextual issues impact implementation; Cost Collection and Analyses Work Group – to measure the practice costs of implementing the MOHR assessment; and Publication, Presentation, and Relations Work Group – to promote opportunities for participants to present and publish findings, coordinate with relevant stakeholder entities, and create a repository of materials, tools, and disseminated findings.

### Intervention

The intervention being studied is the systematic implementation and fielding of the MOHR health behavior and psychosocial assessment, including the delivery of brief customized patient and provider feedback reports. Each local research team worked with their practice pair champions and key stakeholders to determine the most effective workflow for administering the MOHR assessment, including: (a) which patients would be invited to complete the assessment, (b) when the assessment would be completed (*e.g.*, two weeks before a visit, immediately before a visit), (c) where the assessment would be completed (home or practice), (d) whether the assessment would be electronic or paper based, and (e) how clinicians would receive MOHR feedback summaries within the context of office visits. This is consistent with the original NIH consensus panel’s goal of identifying and standardizing patient reported elements to be incorporated into EHRs while minimizing staff burden and enhancing consistency of implementation. As a result, the practice pairs were encouraged to field the electronic version of the MOHR assessment if possible [8].

Because it was not feasible to fully integrate the MOHR assessment into each of the diverse practice’s EHR and patient portal, a stand alone, publically available website (http://www.MyOwnHealthReport.org) was created. The MOHR website is partially integrated with the study practices’ existing EHRs and administers the 17 health behavior and psychosocial screening questions (including basic demographics) as defined by the NIH consensus panel [6,8]. In response to positive depression, anxiety, alcohol, and drug screening questions, the website seamlessly prompts the patient to complete more in-depth assessments, including the Patient Health Questionnaire (PHQ9) [23], the Generalized Anxiety Disorder (GAD) questionnaire [24,25], the Alcohol Use Disorders Identification Test (AUDIT-C) [26], and the Drug Abuse Screening Test (DAST-10) [27], respectively. The MOHR website scores the patient’s responses and characterizes them as being of ‘no concern’ , ‘some concern’, or ‘high concern’ based on norms and national guidelines. For measures with ‘some’ or ‘high concern’ , patients are asked to select which topics they are ready to change and/or discuss with their doctor and select the one topic they feel is most important to address [28-31].

After completing this process, patients are taken to a feedback page to review, download and print (see Figure 3). Health domains in which they are doing well are highlighted and reinforced, initial recommendations for changes and improvements are given for domains where improvements are needed, and space is provided to list any questions, decide on and create up to three SMART goals (specific, measurable, achievable, realistic and timely), and outline follow-up steps to help achieve their goals [32,33]. When patients have finished reviewing their feedback page and leave the website, a clinician summary is also sent to the patient’s primary care team.

**Figure 3 F3:**
[figure not shown]
**Patient summary and feedback from **http://www.MyOwnHealthReport.org**.** The first page demonstrates the patient’s health behavior and psychosocial scores, level of concern, and whether the patient reported readiness to change and interest in talking with their doctor. The second page includes patient workspace for notes, creation of SMART health goals, and a follow-up plan.

### Practice implementation preparation

Practices are being prepared to implement the MOHR assessment through a series of calls and meetings with the site champions, an educational webinar with an interactive ‘call in’ and case scenarios, support materials, and on-site consultation for follow-up. The webinars have been designed using the principles of adult learning, including multiple modalities, reinforcement, modeling and observation. The follow-up consultations have been modeled on academic detailing that entails a brief face-to-face intervention with the clinician, repeated at periodic intervals [34-36]. Academic detailing has been found effective in improving other aspects of clinical care such as cancer screening and chronic disease management [37-43].

The webinars present the evidence supporting the MOHR assessment, strategies for successful practice implementation of risk assessments, and approaches to counseling and supporting patients as they address identified problem behaviors and psychosocial issues. The webinars, as academic detailing, distill the evidence into brief, practical messages that are relevant to and actionable for primary care clinicians. The webinar and local research team consultations seek to change staff attitudes and beliefs toward implementing the MOHR assessment though persuasive communications, including case examples, tailored feedback and reinforcement [44]. Feedback and reinforcement will include weekly practice reports on the number of patients completing the MOHR assessment and bimonthly meetings between practice champions and local research teams to share cross project implementation experiences and review the local implementation process.

### Data sources

Outcomes will be collected from three sources: practice appointment records, the Patient Experience Survey, and patient responses to the MOHR assessment. Appointment records will be used for calculating Reach (see ‘Primary outcomes’, below). Reach measures are collected when practices enter the intervention phase, months two to six for early intervention practices and months seven to nine for delayed intervention practices. Appointment records are queried by the practices (electronically or manually) for patients who meet inclusion criteria, are documented, de-identified, and transferred to a central data coordination center every two weeks. The Patient Experiences Survey will be used to compare the early versus delayed intervention practices on patient reports of patient-provider discussions, recommendations for referrals, and collaborative goal-setting across the 10 health domains. The patient responses to the MOHR assessment will be used for calculating patient health behavior and psychosocial changes over time. This will be assessed by repeated administration of the MOHR assessment for the cohort of patients who complete the assessment on the website and provide email addresses (see ‘Outcomes assessment’ , below).

The content of the Patient Experience Survey and fielding protocol were developed by the working group, building on earlier pilot phase experiences and practice input, with the intention of balancing scientific rigor and patient needs, practice capabilities, and resource availability across the diverse settings. The survey questions were standardized. The 5As framework (Assess, Advise, Agree, Assist and Arrange) served as a guide for developing questions for each health domain [45]. Questions from the Consumer Assessment of Healthcare Providers and Systems (CAHPS) assessing patient trust in their healthcare team and perceived provider communication style were also included [46]. Practices will mail the Patient Experience Survey to patients that the early and delayed intervention practices defined as eligible to receive the MOHR assessment two weeks after the patient’s office visit. To enhance survey response rates, surveys will be mailed using a modified Dillman technique in the practice’s envelope with a cover letter from the patient’s provider [47,48]. Study information will be included with the survey, and completion of the survey will be deemed as consent for participating in the survey – our Institutional Review Board approved a waiver of written consent.

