### Outcomes assessment

The primary outcomes for this study are implementation measures [15]. The measures include the practices’ implementation Reach and Effectiveness [49]. Reach measures include the percent and characteristics of patients that: are defined as eligible to be invited to complete the MOHR assessment; are invited to complete the MOHR assessment; and complete the MOHR assessment. The primary Effectiveness measures are a comparison of early versus delayed intervention practice patient report on whether they: were asked about the health behavior and psychosocial domains; set a goal or action plan with their clinician; and arranged any follow-up contact regarding their plan. As early intervention practices will have implemented the MOHR assessment and delayed intervention practices will not yet have implemented the MOHR assessment, they will respectively serve as intervention and control conditions. The impact on health behaviors and psychosocial problems will be assessed by repeated administration of the MOHR assessment for the subset of patients providing an email address. Patient responses will be compared at baseline and four months after baseline. Multivariate regressions will assess for influences of practice implementation characteristics (*e.g.*, electronic versus paper) and patient demographics on each outcome. The overall CONSORT diagram depicting study participation and data capture are depicted in Figure 4.

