### Trial status

The MOHR trial began January 2013 and is expected to complete data collection in November 2013. The trial is proceeding according to the timeline outlined in Figure 1. Currently, the early implementation clinics are in the early stages of fielding the MOHR assessment to their patients. The delayed intervention clinics will begin implementation between July and September 2013.

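### Reach is collected over unequal, month-numbered windows that do not fit the stated start dates, and the appointment query gives no denominator for percent eligible

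*Protocol article*

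**What the plan says.** The protocol article, under Outcomes assessment, makes implementation measures primary: "The measures include the practices’ implementation Reach and Effectiveness". Reach has three components: percent eligible, percent invited and percent completing. The first is worded: "Reach measures include the percent and characteristics of patients that: are defined as eligible to be invited to complete the MOHR assessment".

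Data sources names appointment records as the source for Reach and fixes when it is collected: "months two to six for early intervention practices and months seven to nine for delayed intervention practices". It also says what is extracted: "Appointment records are queried by the practices (electronically or manually) for patients who meet inclusion criteria". Transfers to the coordinating centre take place every two weeks.

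The start dates appear in three other places. Overall design sets the delay between the groups at four months. The Figure 1 legend, which places the study start in January 2013, says: "The approximate implementation date for the early implementation practices is March 2013 and July 2013 for the delayed implementation practices". Trial status says: "The delayed intervention clinics will begin implementation between July and September 2013". It expects data collection to finish in November 2013.

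On use of the data, Overall design has implementation monitored in both groups. Outcomes assessment plans regressions of each outcome on practice implementation characteristics and patient demographics.

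**The concern.** There are two separate problems.

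The first is the window. It is tied to study months, its length differs between the groups, and it appears to close at month nine even though delayed practices may begin up to September. If the share of patients invited or completing changes as a practice gains experience, a practice observed only in its first weeks will look worse than one observed for five months, even if the two are equally good at each point after go-live. Pooled Reach and any regression of Reach on practice characteristics would then partly describe time since start.

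The second is the denominator. Percent eligible needs a count of everyone seen. The query as worded returns only those who already meet the criteria. The measure is important here because, under Balancing fidelity and adaption, practice pairs choose which patients to target. A narrowly drawn target group can show high completion while few of the practice's patients are reached, and percent eligible is the figure that would show this.

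**Working it through.** **Window length (inclusive count).** Early: 6 − 2 + 1 = 5 months. Delayed: 9 − 7 + 1 = 3 months.

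**Stagger.** Month 7 − month 2 = 5 months. Overall design states 4, and March to July is also 4.

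**Mapping month numbers to dates.** The article does not say whether January 2013 is month 1 or month 0, so both were tried.

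| | January = month 1 | January = month 0 |
|---|---|---|
| Early window | February to June | March to July |
| Months in window for a March start | 4 | 5 |
| Delayed window | July to September | August to October |
| Months in window, July start | 3 | 3 |
| Months in window, August start | 2 | 3 |
| Months in window, September start | 1 | 2 |

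March falls in month 2 only if January is month 0. July falls in month 7 only if January is month 1. No single numbering fits both start dates. Under either one, a September starter has at most one to two months in the window.

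**What the unequal windows could do.** The article gives no Reach figures, so the following is an illustration on assumed values. Let Reach rise linearly from 0 to a plateau P = 50% over R months and then stay there. Mean Reach over a window of T months is P × (1 − R/(2T)) if T ≥ R, and P × T/(2R) if T < R.

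| Time to plateau | 5 months | 3 months | 2 months | 1 month |
|---|---|---|---|---|
| none (constant Reach) | 50% | 50% | 50% | 50% |
| 1 month | 45% | 42% | 37.5% | 25% |
| 2 months | 40% | 33% | 25% | 12.5% |
| 3 months | 35% | 25% | 17% | 8% |

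Example for R = 2: over five months 50 × (1 − 2/10) = 40; over three months 50 × (1 − 2/6) = 33.3; over one month 50 × 1/4 = 12.5. The effect ranges from nothing to large, depending entirely on the unknown time course. The contrast between five and three months is smaller than the contrast between either and a practice truncated at one month.

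**Is change over time plausible?** The article points that way without quantifying it. Practice implementation preparation plans weekly completion reports and repeated follow-up consultations as reinforcement. Cost assessment measures costs once early and again at steady state. No such split is stated for Reach.

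**Denominators.**
- Percent eligible = eligible patients / all patients seen. The query supplies the numerator only.
- Percent invited and percent completed, taken among eligible patients, can both be calculated from the query together with invitation and completion counts.
- Table 2 gives the number of patients seen per year, but these are rounded annual totals. They do not cover the Reach window and say nothing about the characteristics of ineligible patients.

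**The case against.** A reader might infer that the early-versus-delayed comparison of Reach is biased. The documents do not support that: the between-group comparison is stated for the Effectiveness measures only, and Reach is monitored in both groups.

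A reader might also infer that unequal windows by themselves make Reach non-comparable. Reach is a percentage, so a shorter window costs precision and biases it only if Reach changes with time since start or by season. The article gives no evidence of how large such a change would be.

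The design also offers some protection. Target population, timing and mode are chosen by pair, and each pair has one early and one delayed practice. Pair-level choices are therefore balanced across the five- and three-month windows. This stands, and it narrows the concern to the varying delayed start dates, which pairing does not balance.

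The months may be only a nominal schedule. Data sources links collection to a practice entering the intervention phase, Figure 1 calls its dates approximate, and the figure itself is not shown. That is a fair reading of when collection opens. It does not remove the printed end at month nine or say what happens to a late starter.

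On the denominator, the article never states that the inclusion criteria in the query are the same as practice-chosen eligibility, and extraction detail may be fuller elsewhere. The abstract defines Reach only by percent offered and percent completing. These points limit the problem to one of the three Reach measures. They do not supply the missing count.

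**Conclusion.** The point holds in a limited form. As printed, the Reach windows are five months and at most three, their month numbers fit neither the four-month delay nor both start dates, and a late delayed practice could contribute about one to two months to a primary outcome. The last statement assumes that collection stops at month nine.

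The consequence is conditional. With constant Reach there is no bias. With a rise after go-live, pooled Reach and the regressions on practice characteristics would absorb time since start, mainly through the spread of delayed start dates. The size cannot be taken from the article; the illustrated range runs from zero to a several-fold difference for a practice truncated at one month.

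It would go too far to say that Reach has no denominator. Only percent eligible lacks one as the query is worded; percent invited and percent completed remain computable among eligible patients.

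**What to change.** 1. Say which calendar month is month 1, and reconcile the Reach months in Data sources with the four-month delay in Overall design, the dates in Figure 1 and the July-to-September starts in Trial status.
2. Define the Reach window from each practice's own go-live date, and let the delayed window run to the November close of data collection. Report Reach over the longest window common to all 18 practices. Assuming a close on 30 November, this is three months if every practice has started by 1 September and about two months if one starts late in September. Report full-window Reach alongside it and flag truncated practices.
3. Have each practice supply at least the count of all adults seen in its window. Percent eligible can then be reported, as can percent invited and percent completed over all adults seen as well as over eligible patients.

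The change is feasible: the delayed practices had not started when the article was written, and fortnightly transfers already allow data to be aligned to go-live. The cost is a slightly wider query, which is likely to be manual at the two practices without an electronic record (Sites 2 and 3 in Table 2) and would have to be rerun for weeks already past in the early practices. One Reach figure would also rest on a shorter common window, which gives more weight to the start-up period; the full-window figure beside it offsets this.
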